## Abstract

**Background:**

Post-stroke depression (PSD) is one of the most common neuropsychiatric diseases in patients with stroke, and it can increase the disability rate, mortality, and recurrence rate of stroke. Currently, many clinical studies have indicated that traditional Chinese medicine (TCM), such as acupuncture and herbs, Western medicine, rehabilitation, repeated transcranial magnetic stimulation, and other treatment methods, are effective in treating PSD. However, no study has formulated a comprehensive treatment plan that integrates TCM, Western medicine, and rehabilitation for PSD. Thus, this trial aims to assess the efficacy and safety of integrative medicine for treating PSD.

**Methods:**

This multicenter, prospective, randomized, controlled study aims to form a set of effective clinical treatment schemes that integrate TCM, Western medicine, and rehabilitation for PSD. A total of 202 participants recruited from four centers will be randomized into either the integrative medicine or standard care group. Standard care—basic treatment, general nursing care, and exercise therapy—will be provided to all participants. The integrative medicine group will also receive acupuncture, Chinese herbs, and repeated transcranial magnetic stimulation (rTMS). Participants will receive acupuncture and rTMS treatments five times per week for 4 weeks and will be administered Chinese herbs, basic treatment, general nursing care, and exercise therapy for 4 weeks. The primary outcomes include the Hamilton Depression Scale (HAMD), Self-Rating Depression Scale (SDS), and Activity of Daily Living Scale (ADL). And the secondary outcomes include the Montreal Cognitive Assessment Scale, the Fugl-Meyer Assessment (FMA) Scale, and the Pittsburgh Sleep Quality Index (PSQI). All outcome measures will be evaluated at baseline, week 4 (the end of the treatment courses), and week 8 (the end of follow-up). Safety assessments will be performed throughout the study.

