### Blinding

Although unable to blind the intervention operators and participants due to the unique nature of the complex interventions in our trial, the operators, outcome assessors, and statistical analysts will be separated and performed by respective specially-assigned persons, thereby ensuring blinding principles during the process of our clinical trial. The outcome measurement and statistical analyses will be carried out by specially designated researchers who do not know the grouping to avoid possible bias as much as possible.

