### Sample size calculation

The data statistician will carefully compute the appropriate sample size for each group based on the difference in postintervention HAMD scores between the two groups. According to our unpublished pilot study, the HAMD score (mean ± standard deviation) in the standard care group was 16.5 ± 4.51, and the HAMD score in the integrative medicine group was 14.5 ± 3.40. The mean HAMD score in the integrative medicine group was 2 points lower than that in the standard care group. Based on a 5% false-positive error rate (α = 0.05, two-sided, the normal distribution quantile table shows that *Z*_1−α/2_ = 1.96) and 90% power (β = 0.1, the normal distribution quantile table shows that *Z*_1−β_ = 1.28), the sample size is estimated as follows:

$$\begin{array}{l} \begin{array}{l} n=\frac{{\left(Z_{1-\alpha /2}+Z_{1-\beta }\right)}^{2}\times (\sigma_{1}^{2}+\sigma_{2}^{2})}{\delta^{2}}\\ \;=\frac{{\left(1.96+1.28\right)}^{2}\times (3.40^{2}+4.51^{2})}{2^{2}}\approx 83.72 \end{array} \end{array}$$

Each group needs to include 84 participants. Assuming an ~20% dropout rate, a total of 202 participants will be enrolled in this trial.

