#### Standard care group

(1) Basic pharmacological treatment

The specific methods of the basic pharmacological treatment are formulated concerning the *Guidelines for prevention and treatment of cerebrovascular diseases in China (2010 Edition)*. When appropriate, corresponding drugs that have the effect of lipid regulation, blood sugar control, antihypertension, and anticoagulation will be used depending on the patient's primary diseases and complications. The antidepressant drug is paroxetine tablets (Beijing Fuyuan Pharmaceutical Co., Ltd., Guoyao Zhunzi: h20133084) 20 mg, taken orally after meals every morning.

(2) General nursing care

The nursing staff will assess the general condition, psychological status, and family status of the patients. They will also strengthen guardianship, communicate with the patients, reduce insecurity of the patients, and prevent unsafe incidents such as suicide. Nursing care will be provided to keep the patients' sleep, diet, and environment comfortable.

(3) Exercise therapy

A professional therapist will assess the patient's Brunnstrom stage. In accordance with the impairment of the patient's motor functions (e.g., muscle tone, muscle strength, balance, movement coordination, and proprioception), an individualized scheme of exercise therapy will be developed. The scheme of exercise therapy includes proper limb positioning, joint range-of-motion training, muscle strength training, turnover, transfer training, sitting, standing balance training, gait training, and so on. One session will last for 30–45 min. The treatment frequency and treatment course of exercise therapy will be once a day for 4 weeks (Yu and Park, 2013; Bang and Son, 2016).

Standard care (including basic pharmacological treatment, general nursing care, and exercise therapy) is a fundamental treatment for stroke and PSD. It is worth noting that after receiving 4 weeks of the aforementioned standard care in both the integrative medicine and standard care groups, specialist physicians will determine whether such standard care approaches should be continued based on the individual recovery conditions.

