### Outcome measures

#### Primary outcomes

The primary outcome will be measured at baseline, week 4 after treatment, and week 8 during follow-up.

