##### Self-rating depression scale

The self-rating depression scale was developed by W.K. Zung in 1965. It can reflect the depressive state and its variability well (Zung, 1965). The scale contains 20 items scored on a 4-point scale. The rough scores were obtained by summing each of the 20 new items, multiplying the rough scores by 1.25, and then taking the integer part as the standard score. A standard score of 50–59 is considered to be a mild depressive mood, a standard score of 60–69 is considered to be moderate depression, and a standard score of more than 70 is considered to be severe depression. Patients respond according to their situation in the past week.

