### Statistical analysis

Statistical analyses will be carried out by statisticians unaware of the groupings. The statistical analysis will be performed using SPSS software version 25.0. A two-sided 5% significance level will be adopted, and the corresponding 95% CI will be calculated to the greatest extent possible. A *p*-value of <0.05 will be set as the significance level.

Demographic characteristics and baseline measurements of the variables in each group will be summarized. Measurement data that conform to a normal distribution will be displayed using the mean ± SD, while the median, minimum, and maximum will describe measurement data that do not conform to a normal distribution. To assess the treatment effectiveness, outcome measurement data at baseline, after the intervention, and follow-up (i.e., 4 and 8 weeks), will be analyzed. For the qualitative data, the difference between and within groups will be tested by the chi-square or Fisher's exact test. For quantitative data, either parametric tests (Student's *t*-test) or non-parametric tests (Mann–Whitney *U*-test, Wilcoxon signed-rank test) will be used, depending on the normality of the distribution. In addition, the intention-to-treat analysis will be carried out to minimize potential attrition bias.

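### Three unranked primary outcomes, analysed at two visits and each tested at an undivided 5%, do not fit a sample size that spends the whole 5% and 90% power on post-treatment HAMD alone

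*Protocol article*

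**What the plan says.** - **Which outcomes are primary.** Abstract, Methods: "The primary outcomes include the Hamilton Depression Scale (HAMD), Self-Rating Depression Scale (SDS), and Activity of Daily Living Scale (ADL"). No order is given. The Primary outcomes section and Table 1 list the same three, again unranked.
- **When they are measured.** Abstract: "All outcome measures will be evaluated at baseline, week 4 (the end of the treatment courses), and week 8 (the end of follow-up"). Primary outcomes section: "The primary outcome will be measured at baseline, week 4 after treatment, and week 8 during follow-up". The Statistical analysis section says that the 4- and 8-week data will be analysed. Neither visit is called primary. Table 1, as it reads in the extracted text, marks week 8 for HAMD and ADL but not for SDS.
- **How they are tested.** Statistical analysis: "A two-sided 5% significance level will be adopted", with p<0.05 as the threshold and separate parametric or non-parametric tests for quantitative outcomes.
- **What was sized.** The sample size is "based on the difference in postintervention HAMD scores between the two groups", at a two-sided 5% and 90% power: 84 per group, and 202 in total after a dropout allowance of about 20%.

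**The concern.** A sample size calculation at the full 5% and 90% power for one variable makes sense only if that variable decides the trial alone. The article instead gives three variables equal standing and analyses each at up to two visits at the same 5%. It fixes no success rule.

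What is at stake is what counts as a positive trial. As written, one p<0.05 among up to six comparisons could be reported as efficacy on a primary outcome, even if HAMD at week 4, the only comparison that was sized, showed nothing. If all three were required instead, the trial could fail with a probability well above the 10% that the stated power implies.

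**Working it through.** **1. The article's own sample size.** Inputs from the Sample size calculation section: SDs 3.40 and 4.51, difference 2, normal quantiles 1.96 and 1.28.

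n = (1.96 + 1.28)² × (3.40² + 4.51²) / 2² = 10.4976 × 31.9001 / 4 = 83.72, so 84 per group. The stated figure reproduces.

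Power with 84 per group: 2 / √(31.9001/84) = 3.245; 3.245 − 1.960 = 1.285; power = 90.1%. This is the power of one HAMD test at 5%.

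**2. If any one significant result counts as success.** With k independent tests at 5%, the family-wise error is 1 − 0.95^k:

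- 3 tests (three outcomes, one visit): 14.3%
- 5 tests (SDS not taken at week 8): 22.6%
- 6 tests (three outcomes, two visits): 26.5%

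Independence is the upper end, because two depression scales and repeated visits in the same patients will be correlated. The article gives no correlations, so they are assumed here. The table comes from multivariate-normal simulation with 2,000,000 draws, an equal correlation between outcomes, and 0.7 between visits:

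| Outcome correlation | 3 tests | 5 tests | 6 tests |
|---|---|---|---|
| 0.3 | 13.6% | 19.4% | 22.0% |
| 0.5 | 12.6% | 18.0% | 20.2% |
| 0.7 | 11.0% | 15.9% | 17.7% |
| 0.8 | 9.8% | 14.5% | 15.9% |

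Taken with the independence figures, the ranges are about 10-14% (three tests), 14-23% (five) and 16-26% (six). The lower ends depend on the assumed structure: a common correlation of 0.8 among all six tests gives 13.8%.

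**3. If all three outcomes must succeed.** The type I error is at most 5%. If each test had 90% power (an assumption, since no power is given for SDS or ADL), joint power at one visit would be 0.9³ = 72.9% at correlation 0, about 78% at 0.5 and about 81% at 0.7.

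**4. If the 5% is split equally (Bonferroni).** For the same HAMD effect:

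| Tests | Level per test | HAMD power at 84 per group | n per group for 90% |
|---|---|---|---|
| 1 | 0.05 | 90.1% | 84 |
| 3 | 0.0167 | 80.3% | 108 |
| 6 | 0.0083 | 72.8% | 123 |

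**5. Comparison.** Any-one-wins breaks the 5%. All-must-win and an equal split each break the 90%. Of the readings examined, only HAMD after treatment as the sole deciding test keeps both, and that is not what the outcome sections say.

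**The case against.** **A statistical analysis plan may hold the rule.** This is a condensed article, and a success rule or multiplicity procedure is often left to a fuller document. Silence on such a procedure is therefore not the fault. What stands is the set of positive statements: three primary outcomes, one undivided 5%, and a sample size that uses all of that 5% on one outcome. A later document could settle the matter only by narrowing the primary set or by giving up the stated error rate or power.

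**HAMD may be meant as decisive, with SDS and ADL in support.** This is plausible and fits the sample size section, but the outcome sections say otherwise. The fix adopts it.

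**The error rates are conditional.** A reader might infer that the trial's false-positive rate simply is some figure between 12% and 26%. The documents do not support that. They state no any-one-wins rule, the 26% end needs independence, and 12% is not a floor, since three tests at correlation 0.8 give 9.8%. The joint-power figures are likewise hypothetical.

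**The number of tests is uncertain.** The Abstract and the Primary outcomes section imply six. Table 1 as extracted suggests five, though the table may have been damaged in extraction. Either count leaves the conclusion unchanged.

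**Two further inferences go too far.**

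- A reader might take the SDS, for which "Patients respond according to their situation in the past week", to contradict the Blinding section's statement that "The outcome measurement and statistical analyses will be carried out by specially designated researchers who do not know the grouping". That section also says openly that participants cannot be blinded, the Data collection and management section has psychiatrists complete both HAMD and SDS, and the Discussion concedes the subjectivity of patient-reported scales. HAMD also draws on answers from unblinded patients, so the contrast between the two is one of degree.
- A reader might also hold the week-8 comparison invalid because, after week 4, "specialist physicians will determine whether such standard care approaches should be continued based on the individual recovery conditions". That provision applies to both arms, and the comparison can be read as one of treatment policies.

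Both are matters for reporting.

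**Conclusion.** The point holds: the primary outcome set, the error level and the sample size do not fit together as written. The size depends on a success rule that the article does not state:

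- **Any one success suffices:** family-wise error about 10-14% (three tests at one visit) or 16-26% (six tests at two visits), and about 14-23% for five tests. The ranges run from an assumed outcome correlation of 0.8, with 0.7 between visits, up to independence.
- **All three must succeed:** error at or below 5%, but joint power about 73-81% for correlations 0-0.7, assuming 90% power for each test.

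The inconsistency itself needs none of these assumptions. It matters because it leaves open what would count as success, and a choice made after the results are seen by arm would be data-driven.

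**What to change.** Name HAMD at week 4 as the single primary outcome. This agrees with the Sample size calculation section and keeps 84 evaluable per group, about 90% power and a 5% error rate. Make SDS, ADL and all week-8 results secondary, tested in a fixed order or by Holm, and only if HAMD at week 4 succeeds. Settle this before any outcome data are seen by arm.

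Reconcile Table 1 with the Abstract and the Primary outcomes section on whether SDS is taken at week 8.

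As reporting notes only: describe SDS as self-reported by participants who know their allocation, and report week 8 as a treatment-policy comparison, with standard care received after week 4 tabulated by arm.

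The cost is a wording amendment, with no extra patients or visits. The registry record is not at hand, so its outcome list should be checked for agreement. The one small loss is that SDS and ADL can no longer carry the efficacy claim alone.

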**Discussion:**

This study is expected to verify the efficacy and safety of integrative medicine for treating PSD, providing an evidence-based clinical reference for the future development of a standardized scheme.

**Clinical trial registration:**

ClinicalTrials.gov, identifier: NCT05187975

## Introduction

Stroke has become the world's second most common cause of death (Mozaffarian et al., 2016). According to comprehensive global, regional, and national stroke lifetime risk data, the lifetime risk of stroke for people aged 25 or more in 2016 was 24.9% (Feigin et al., 2018). The overall risk of lifelong stroke in the Chinese population is as high as 39.3% (Wang et al., 2019). Moreover, post-stroke depression (PSD) is the most frequent neuropsychiatric sequela of stroke. Many patients suffer from depression after a stroke. Statistically, the incidence varies from one study to another, with the estimated frequency of PSD being 31% (Hackett and Pickles, 2014).

Antidepressants are currently the main treatment for depression. However, the side effects of Western drugs on the human nervous system, digestive system, liver, and biliary system are inevitable. Nonpharmacological interventions include psychotherapy, exercise therapy, acupuncture, and noninvasive brain stimulation, among others (Lanctôt et al., 2020). Acupuncture has been demonstrated to be beneficial for treating PSD. For example, a previous meta-analysis found that in conjunction with conventional acupuncture, scalp acupuncture can improve depression and promote the activities of daily living (ADLs) in PSD patients, thereby indicating that acupuncture may be a promising therapy for PSD (Hang et al., 2021). Traditional Chinese medicine (TCM), such as Chinese herbs, has certain curative effects on the depressive state, neurological deficits, and daily living ability of PSD patients. Clinically, liver-Qi stagnation is one of the most common syndrome patterns of PSD according to the TCM syndrome patterns. The Chinese herb “Chaihu Shugan Powder” is one of the representative formulas for treating liver-Qi stagnation syndrome. Previous studies have reported that Chaihu Shugan powder could relieve the depressive state in patients with PSD (Tao, 2015; Yuan, 2018). In addition, repeated transcranial magnetic stimulation (rTMS) is recognized by the U.S. Food and Drug Administration (FDA) because it is safe and effective with minimal side effects (Perera et al., 2016), and depression is a recommended indication of rTMS (Level A evidence) (Lefaucheur et al., 2020). In addition, rTMS effectively improves the daily living ability and cognitive function of patients with PSD (Shen et al., 2017). Thus, it is anticipated that the above TCM therapies and rTMS can broaden the treatment approach for PSD. Meanwhile, they can bring adjunctive therapeutic effects to conventional treatments with enhanced safety profiles. Thus, they may be worthy of clinical applications and vigorous development.

In reference to the previous literature, most clinical studies have reported that when a specified TCM or rehabilitation therapy is combined with drug therapy or other active treatments, such integrated approaches can generally lead to higher efficiency and fewer adverse effects (Wen et al., 2016; Qiao et al., 2020). The advantage of integrative medicine is that it makes full use of all appropriate therapeutic approaches (including conventional and complementary therapies), health care professionals, and disciplines to achieve optimal efficacy. Nonetheless, despite its potential superiority, the concept of “integrative medicine” is often underestimated, and to date, clinicians have not taken full advantage of integrative medicine in clinical settings (Liu et al., 2019).

Taken together, we designed this multicenter, prospective, randomized, controlled study to assess the efficacy and safety of integrative medicine on PSD, which integrates TCM, Western medicine, and rehabilitation treatment. To the best of our knowledge, this is the first study to involve a combination of multiple well-established rehabilitation therapies for PSD under the increasingly popular concept of integrative medicine. It is expected that our study will contribute to forming a standardized treatment scheme of integrative medicine for PSD in the future.

## Methods

### Study design

This study is designed as a multicenter, prospective, parallel-group, randomized, controlled trial (RCT). All eligible participants will be randomly assigned to either the integrative medicine or standard care group. The study duration will be 12 weeks, which consists of a 4-week treatment period and an 8-week follow-up period. The research flow chart is displayed in Figure 1, and the trial schedule of enrollment, treatments, and assessments is displayed in Table 1. The reporting of this protocol is strictly based on the Standard Protocol Items: Recommendations for Interventional Trials (SPIRIT) (Chan et al., 2013).

**Figure 1 F1:**
[figure not shown]
Flowchart of the trial. rTMS, Repeated Transcranial Magnetic Stimulation; HAMD, Hamilton Depression Scale; SDS Self-Rating Depression Scale; ADL, Activities of Daily Living; MoCA, Montreal Cognitive Assessment scale; FMA, the Fugl-Meyer Assessment of Motor Function Scale.

**Table 1 T1:** Schedule of enrollment, treatments, and assessments.

**Time (weeks)**	**W-1**	**W 0**	**W 1**	**W2**	**W3**	**W4**	**W 8**
**Period assessment**	**Screening**	**Baseline**	**Intervention**				**Follow-up**
**Patients**
Screening	×						
Informed consent	×						
Demographic data		×					
Disease history		×					
Randomization		×					
**Intervention**
Integrated rehabilitation group (*n* = 101)			Acupuncture TCM rTMS add the same treatment of the standard care group				
Standard care group (*n* = 101)			Basic disease treatment General care Exercise therapy				
**Primary outcomes**
HAMD		×	×				×
SDS		×	×				
ADL		×	×				×
**Secondary outcomes**
MoCA		×	×				
PSQI		×	×				×
FMA		×	×				
Adverse events			×	×	×	×	×
Causes of dropout			×	×	×	×	×

### Ethical approval and study registration

This study was approved by the Medical Ethics Committee of the Third Affiliated Hospital of Zhejiang Chinese Medical University and registered with the ClinicalTrials.gov database (NCT Number: NCT05187975).

### Patients and enrollment

#### Diagnostic criteria

Participants should meet the diagnostic criteria of cerebral infarction (Rao, 2010) or cerebral hemorrhage (Rao, 2010) in combination with depressive disorders (Psychiatry CSo, 2001). Meanwhile, the TCM syndrome pattern should meet the diagnostic standard (Yu and Fang, 2018) of liver-Qi stagnation syndrome according to the following aspects:

(1) qualified tongue and pulse conditions of TCM: the patient has a pale red tongue, thin and greasy moss, and a wiry pulse;(2) primary symptoms and signs include mental depression, emotional disturbance, frequent sighing, thoracic oppression, fullness, or distending pain in the hypochondrium, migratory pain, and epigastric distention; and(3) secondary symptoms and signs include no appetite, irregular bowel movements, and irregular menstrual periods (for females);

With the qualified tongue and pulse conditions, if a patient has three primary symptoms/signs or two secondary symptoms/signs combined with two primary symptoms/signs, they may be diagnosed with liver-Qi stagnation syndrome.

